# Autologous cord blood mononuclear cell infusion for the prevention of bronchopulmonary dysplasia in very preterm monozygotic twins: A study protocol for a randomized, placebo-controlled, double-blinded multicenter trial

**DOI:** 10.3389/fped.2022.884366

**Published:** 2022-12-09

**Keywords:** cord blood mononuclear cells, bronchopulmonary dysplasia, very preterm monozygotic twins, prevention, autologous, study protocol

## Abstract

**Background:**

Preterm-associated complications remain the main cause of neonatal death. Survivors face the challenges of short- and long-term complications. Among all complications, bronchopulmonary dysplasia (BPD) remains the first important cause of neonatal mortality and morbidity. Current treatment does not address this main preterm complication. Cord blood is regarded as a convenient source of stem cells. The paracrine bioactive factors of stem cells contribute to tissue repair and immune modulation. Our clinical studies and those of others have shown that cord blood cell infusion is both safe and possibly effective in the prevention and treatment of BPD. The therapeutic use of cord blood has emerged as a promising therapy. However, the genetic heterogeneity between control and intervention groups may reduce the comparability especially among small sample trials. The purpose of this study protocol is to investigate the effects of autologous cord blood mononuclear cell (ACBMNC) infusion on the prevention of BPD in very preterm monozygotic twins of less than 32 gestation weeks.

**Methods:**

In this prospective, randomized, placebo-controlled, double-blinded multicenter clinical trial, 60 pairs of monozygotic twin preterm neonates of less than 32 weeks admitted to the Neonatal Intensive Care Unit are randomly assigned to receive intravenous ACBMNC infusion (targeted at 5 × 10^7^ cells/kg) or placebo (normal saline) within 24 h after birth in a 1:1 ratio. The primary outcome will be survival without BPD at 36 weeks of postmenstrual age. The secondary outcomes will include the mortality rate, BPD severity, other common preterm complication rates, respiratory support duration, length and cost of hospitalization, and long-term respiratory and neurodevelopmental outcomes during a 2-year follow-up. Furthermore, we will perform single-cell RNA sequencing for cord blood cells and blood cells 3–10 days after intervention and detect whether reactive oxygen species and inflammatory cytokines are present.

**Conclusion:**

This will be the first randomized, placebo-controlled, double-blinded trial to evaluate the efficacy of ACBMNC infusion to prevent BPD in monozygotic twin premature infants and investigate the underlying protective mechanisms. The results of this trial will provide valuable clinical evidence for translational application of cord blood cell therapy in very preterm infants.

**Trial registration:** ClinicalTrials.gov, NCT05087498, registered 10/09/2021, https://register.clinicaltrials.gov/prs/app/action/SelectProtocol?sid=S000BAD7&selectaction=Edit&uid=U0002PLA&ts=2&cx=qvyylv.

## Introduction

Preterm births and their complications are the leading cause of death for children under 5 years old (1). Preterm-associated lifetime disability, including intellectual and physical disability, and chronic lung disease, contributes to a huge social burden (2–4). Intensive care therapy in the Neonatal Intensive Care Unit (NICU) has seen great advances in recent years; however, the long-term morbidity rate has not shown any improvement. Inversely, given the higher survival rates of very preterm neonates, the incidence of bronchopulmonary dysplasia (BPD) increases (2, 5, 6). Fragile preterm neonates experience persistent tissue injury and insufficient repair because of their immature organs and various invasive therapies that they are subjected to after birth (6, 7). The immature lung is the main organ that is commonly affected. Alveolar simplification and dysregulated vascularization are the main characteristics of BPD (3, 7, 8). Current treatments do not address the underlying pathological process of this main preterm complication (3, 5, 9).

Stem cell therapy has shown promising potential in supporting tissue development and cell repair and is rapidly emerging as a novel therapeutic tool for several neonatal diseases (10–12). Human umbilical cord blood cells (HUCBCs) are abundant in stem cells (13, 14). These primitive cells can produce anti-inflammatory, anti-apoptotic, and immunoregulatory bioactive factors through paracrine effects and stimulate endogenous cell repair (15, 16). Preclinical studies have demonstrated the effect of cord blood stem cell infusion on the prevention and treatment of BPD (15, 17). Evidence from our clinical trials and the trials of several others has proved the safety, feasibility, and potential effect of umbilical cord blood (UCB)-derived stem cell administration in preterm neonates as well as long-term safety (18–21). However, the current trials often suffer from a small sample size, and the final statistical analysis results of the main outcomes show no significant difference between the cord blood cell intervention group and the control group (18–21).

Both genetic predisposition and intervention difference between individuals affect the clinical outcomes of patients (6, 22). To increase the statistical potency of the therapeutic effect of cord blood stem cells especially among small sample trials, enrolling very preterm monozygotic twins of less than 32 gestation weeks (GW) could improve the comparability between intervention and control groups as the hereditary material is the same within monozygotic twins.

With these concepts in mind, here, the authors will enroll very preterm monozygotic twins and assign the random number. Therefore, one of the twins will be assigned to the control group and the other to the intervention group. Furthermore, we will perform single-cell RNA sequencing for cord blood cells and blood cells 3–10 days after intervention and detect whether reactive oxygen species and inflammatory cytokines are present in serum from abandoned blood samples. As the genetic background is the same within monozygotic twins, the results of single-cell RNA sequencing are expected to have better comparability, following which the mechanisms elucidated will reveal the effect of autologous cord blood mononuclear cell (ACBMNC) infusion to the maximum (23). This will be the first randomized, placebo-controlled, and double-blinded trial to evaluate the efficacy of ACBMNC infusion as a prophylactic measure for BPD in monozygotic twin premature infants who have the same genetic background and investigate the underlying protective mechanisms *via* single-cell RNA sequencing.

## Methods

### Study design and settings

This study protocol describes a randomized, placebo-controlled, double-blinded, and multicenter trial to be conducted at seven medical centers (Guangdong Women and Children Hospital, Dongguan Maternal and Child Health Hospital, Zhongshan Boai Hospital, Shunde Hospital-Southern Medical University, Dongguan Hospital-Southern Medical University, Nanfang Hospital-Southern Medical University, and Affiliated Maternal and Child Hospital of Foshan-Southern Medical University) in tertiary hospitals. The participating NICUs are selected by an expert committee based on the distance to the Guangdong Cord Blood Bank (GDCBB) and the level of intensive care that these NICUs could provide. The Guangdong Cord Blood Bank is a public provincial blood bank affiliated with the Guangdong Women and Children Hospital and collects cord blood routinely at these enrolled hospitals. To ensure that the cord blood is processed and infused to infants within 24 h after birth, the distance between these centers should be short. Furthermore, to reduce the differences in therapeutic treatment between the selected centers, a uniform guideline regarding the treatment of patients has been devised in all clinical centers. These centers hold quality control meetings every 3 months to ensure research consistency and report and analyze the possible side effects caused by MNC infusion. In this study, a total of 60 pairs of monozygotic twin premature infants fulfilling the eligibility criteria will be enrolled. For each pair, one random number will be assigned to the first baby of the twins; if the last digit of this random number is odd, the first baby will be assigned to the intervention group, and the second baby will be automatically assigned to the control group; in contrast, if the last digit of this random number is even, the first baby will be assigned to the control group, and the second will be automatically assigned to the intervention group. The protocol for this study has been developed based on the Standard Protocol Items: Recommendations for Interventional Trials (SPIRIT) checklist (Supplementary material S1, S2). We have followed the Consolidated Standards of Reporting Trials (CONSORT) guidelines and the study design is illustrated in Figure 1.

**Figure 1 F1:**
[figure not shown]
Consort flow diagram.

## Trial objectives

### Primary objective

The primary objective of this trial is to evaluate the efficacy of ACBMNC infusion for the prevention of BPD in very preterm monozygotic twins of less than 32 GW.

### Secondary objectives

The secondary objectives of this trial are as follows: (1) to compare the infant mortality rate at 36 weeks of postmenstrual age; (2) to compare the rates of other common preterm complications such as intraventricular hemorrhage (IVH), necrotizing enterocolitis (NEC), retinopathy of prematurity (ROP), respiratory distress syndrome (RDS), ventilation-associated pneumonia (VAP), hypoxic ischemic encephalopathy (HIE), late-onset sepsis (LOS), periventricular leukomalacia (PVL), and anemia; (3) to compare the duration of mechanical ventilation and oxygen therapy in the two groups; (4) to determine the re-intubation rate and time of return to birth weight (BW); (5) to compare the duration of antibiotic usage; (6) to determine the long-term outcomes during a 2-year follow-up, including anthropometric characteristics, respiratory outcomes, and neurodevelopmental outcomes *via* a standardized neurological examination; (7) to compare the results of single-cell RNA sequencing for cord blood cells and blood cells 3–10 days after intervention and detect whether reactive oxygen species and inflammatory cytokines are present in serum.

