### Sample size

Our previous study showed that ACBMNC infusion was effective in reducing respiratory support duration in preterm infants (18). A randomized study in Korea by Won Soon Park showed that severe BPD incidence significantly reduced from 53% to 19% with mesenchymal stem cell intervention in the 23–24 GW group (*n* = 33) (20). The rate of BPD among very preterm infants at our NICU was 30% (pA), which is similar to the incidence rate reported previously (26). The sample size of this study was determined for assessing the efficacy of ACBMNCs compared with placebo with respect to the primary outcome in order to decrease the incidence of BPD or death with a two-sided α level of 0.05% and 80% power. We expect the intended (or at least acceptable) effect of ACBMNC infusion to be at a rate of 20% decrease in the frequency of BPD. To achieve this rate, at least 60 patients per group will be required based on the following formula:n=(pA(1−pA)/κ+pB(1−pB))((z1−α/2+z1−β)/(pA−pB))2)

κ = nA/nB is the matching ratio; α is type I error; β is type II error, meaning 1 − β is power.

Around 20 pairs of monozygotic twin births of less than 32 gestational weeks occur annually in Guangdong Women and Children Hospital and Dongguan Maternal and Child Health Hospital. Around 6 pairs of monozygotic twin births of less than 32 gestational weeks take place annually in Zhongshan Boai Hospital, Shunde Hospital, Southern Medical University, Dongguan Hospital, Southern Medical University, Nanfang Hospital, Southern Medical University, and Affiliated Maternal and Child Hospital of Foshan, Southern Medical University. Therefore, we assume that 60 pairs of monozygotic twins will be enrolled annually and the trial could be completed within 1 year.

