### Outcome measures

Primary outcome:
– Surviving without BPD.Secondary outcomes:
– Surviving without severe preterm-associated complications (severe BPD, severe ROP, and severe IVH).– Mortality rate.– BPD severity.Other outcomes:
– Incidence of other preterm complications including IVH, PVL, NEC, ROP, RDS, VAP, LOS, and anemia.– Duration of mechanical ventilation and oxygen therapy.– Frequency of re-intubation.– The time (days) to return to BW.– Body weight during the first 4 weeks (measured on each week).– Duration of hospitalization.– Hospitalization expenses.We will use the following clinical definitions in this study: (all clinical diagnoses will be defined according to a standard reference) (30).
1.GA will be determined on the basis of a combination of the last menstrual period and early ultrasound findings.2.The diagnosis of common preterm complications will include the following:

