### Follow-up

All infants will be followed up three times (corrected GA of 40 weeks and corrected age of 12 and 24 months), and the following parameters will be recorded.

*Follow-up content at corrected GA of 40 weeks:*
– Main caregiver and the education level.– Smoking in main caregivers.– Feeding mode (breastfeeding, formula, and mixed feeding).– Anthropometric characteristics: weight, length, and head circumference.– Respiratory outcomes: the occurrence of wheezing, supplemental oxygen requirement, and rehospitalization because of pneumonia.– Neurodevelopmental outcome: neonatal behavioral neurological assessment score, the occurrence of seizure, encephalomalacia, intracranial hemorrhage, and auditory and visual impairment.– Results of blood routine examination.*Follow-up content on corrected age of 12 and 24 months:*
– Anthropometric characteristics: weight, length, head circumference, and anterior fontanel size.– Respiratory outcomes: the occurrence of wheezing, asthma, nocturnal cough, supplemental oxygen requirement, and rehospitalization because of pneumonia.– Degree of neurodevelopmental impairment *via* standardized neurological examination (using the Bayley scales) and other major neurodevelopmental outcomes such as cerebral palsy, seizures, auditory impairment, and visual impairment.– Results of blood routine examination.

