### Statistical analysis

Mean and standard deviation are reported for continuous variables, and the number and percentage are reported for categorical variables. Group comparisons of categorical variables for outcomes and co-interventions including death, BPD, and BPD severity are performed using nonparametric tests, the Fisher's exact test, or chi-square test, as appropriate. The relative risk (RR) is calculated as the ratio of the cumulative incidence rates of an event occurring in the intervention infusion group to the control group, and the number needed for treatment as the inverse of these two cumulative incidence rates. The results are shown as RR with 95% confidence interval (CI). For continuous variables, the mean values at each time point in each group of the variables are derived from a generalized linear model and the differences in the values over time are compared using an unpaired Student's t-test between the two groups. Kaplan–Meier cumulative incidence plots are generated to show time-to-event end points, namely, extubation and weaning to room air. All statistical tests are two-tailed, and *p*-values < 0.05 are deemed statistically significant. The Breslow–Day test and Cochran–Mantel–Haenszel (CMH) test will be used to adjust the data derived from different participating centers. The results will be reported as odds ratio (OR) with 95% CI. All statistical tests will be two-tailed and a *p*-value < 0.05 will be considered statistically significant. All statistical analysis will be performed using SPSS 21.0 (IBM).

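### Durations and expenses that death can cut short are compared by means and a t-test with no rule for deaths, so the comparison is biased if mortality differs between arms

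*Protocol article*

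**What the plan says.** All references are to the protocol article.

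- **Secondary objectives** include "to compare the duration of mechanical ventilation and oxygen therapy in the two groups" and a comparison of antibiotic duration. Mortality at 36 weeks is a separate objective.
- **Outcome measures** places ventilation and oxygen duration, "Duration of hospitalization" and hospital expenses under other outcomes, below the secondary ones. The Abstract, by contrast, counts respiratory support duration and the length and cost of stay among the secondary outcomes.
- **Statistical analysis** states "Mean and standard deviation are reported for continuous variables, and the number and percentage are reported for categorical variables". Means come from a generalized linear model, and "differences in the values over time are compared using an unpaired Student's t-test between the two groups". No other test is named for a continuous variable.
- The same section adds "Kaplan–Meier cumulative incidence plots are generated to show time-to-event end points, namely, extubation and weaning to room air". It attaches no test to these plots and does not say how a death before extubation or weaning is treated.
- **Sample size** cites the group's earlier study, in which the infusion was "effective in reducing respiratory support duration in preterm infants".

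**The concern.** Death is foreseen in this trial. Only infants thought unlikely to live through the first day are excluded, death is a listed severe adverse event, and mortality is an outcome. The primary outcome already combines survival with freedom from BPD, because BPD cannot be judged apart from death. The duration and cost outcomes have no such protection.

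An infant who dies on day 5 can have at most 5 ventilator days and 5 days of stay, and will probably have a small bill. Entered as observed, these are among the most favourable values in the trial. If the treatment changes survival, the difference in means then mixes recovery with death. Shorter respiratory support is the effect the sponsor cites from its own earlier work, so a duration result that cannot be interpreted would be a real loss.

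**Working it through.** **Plan's own figure.** There is none for these outcomes: no mortality rate, mean duration or SD is given. The one computed figure, 60 per group, belongs to the primary outcome. It reproduces as 59 from the printed formula with 0.30 against 0.10, two-sided alpha 0.05 and 80% power, and has no bearing here. Everything below except 60 per arm is an assumption.

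**1. Deaths keep their observed values.**

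Arm mean = (1 − p) × survivor mean + p × mean at death, where p is mortality. With no effect in survivors:

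Shift (treated − control) = (p control − p treated) × (survivor mean − mean at death)

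Assume survivors average 40 oxygen days and 60 hospital days, and deaths average day 7.

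| Mortality difference | Oxygen days | Hospital days |
|---|---|---|
| 0 points | 0 | 0 |
| 2 points | 0.02 × 33 = 0.66 | 0.02 × 53 = 1.06 |
| 6 points (10% v 4%) | 0.06 × 33 = 1.98 | 0.06 × 53 = 3.18 |
| 8 points | 0.08 × 33 = 2.64 | 0.08 × 53 = 4.24 |

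Each figure is the number of days by which the treated arm looks worse.

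**2. A real benefit can be hidden.** Let treatment shorten oxygen in survivors from 40 to 37.6 days, with mortality 10% v 4%:

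- treated: 0.96 × 37.6 + 0.04 × 7 = 36.38
- control: 0.90 × 40 + 0.10 × 7 = 36.70

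The difference is 0.32 days, against 2.4 days in survivors.

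**3. Chance of a misleading test.** This was simulated with 60 independent infants per arm and 20,000 runs. Survivors averaged 30 days (gamma, shape 4) in both arms and deaths averaged 5 days. The last column scores support-free days out of 60, with death as 0.

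| Mortality, control / treated | Mean difference (days) | Significantly longer on treatment | Support-free days, treated − control |
|---|---|---|---|
| 10% / 10% | 0 | 2.5% | about 0 |
| 10% / 5% | +1.25 | 6.4% | +1.5 |
| 15% / 5% | +2.5 | 13.2% | +3.1 |
| 20% / 5% | +3.75 | 24.3% | +4.5 |

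Where treatment saves lives, the raw mean counts against it and the support-free scale counts for it.

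**4. Survivors only.** At 10% v 4%, expected deaths are 0.10 × 60 = 6 and 0.04 × 60 = 2.4. Up to 8.4 of 60 pairs (14%) would lose one twin, and the infants left are selected by an event after randomisation.

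**5. Kaplan–Meier plots.** Suppose 6 of 60 infants die before extubation and the other 54 are later extubated. The true cumulative incidence is 54/60 = 90%. If the deaths are censored, the curve still climbs to 100%. An arm with 4% mortality also reaches 100% against a true 96%, so the plot hides the difference.

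**The case against.** Several parts of the case against this point stand.

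- **Ventilation and oxygen are not left to means alone.** The plots of extubation and weaning address the same two processes, and there a death need not count as early success. But with no test and no death rule they do not settle the matter, and antibiotics, stay and expenses have no such display.
- **The t-test sentence may be meant for repeated measures.** Its reference to values over time fits weekly weight better than a single duration. It is still the only test named for any continuous variable.
- **The handling of deaths is not stated.** A reader might infer that the plan enters deaths at their short values. The text does not say so; survivors-only is equally open, and an analysis plan that is not shown could set the rule. The point is therefore not the omission by itself. The comparison that is named does not suit these outcomes under either of those readings.
- **Discharge on oxygen.** A reader might also infer that oxygen duration is cut off at discharge, because Follow-up records "supplemental oxygen requirement, and rehospitalization because of pneumonia". Nothing in the text says that duration stops at discharge, so this is not part of the point.
- **Rank and context.** Outcome measures lists most of these as other outcomes and omits antibiotic duration. Death also appears in the primary outcome and on its own, so a misleading duration would not stand unaccompanied.

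**Conclusion.** The point holds in a limited form. The named comparison, means with an unpaired t-test, gives a biased or selected contrast for outcomes that death truncates, and the added Kaplan–Meier plots do not repair it. If deaths keep their short values, the bias runs against the arm with better survival. It is about 0.7 to 4.2 days for mortality differences of 2 to 8 points, with assumed survivor means of 40 and 60 days and death at day 7 on average. It is zero if mortality is equal.

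The document does not support the stronger conclusion that the plan will show an effective treatment as harmful, or a harmful one as beneficial. That needs a mortality difference and a particular handling of deaths, neither of which can be read from the text. At 10% v 5% mortality the simulated chance of a significant wrong-direction result is 6.4%, against 2.5% with equal mortality. No primary conclusion is affected. The analysis should still be changed, because the change is cheap and the result is one the sponsor has reason to quote.

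**What to change.** Amend the Statistical analysis section as follows.

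1. **Ventilation:** compare ventilator-free days to day 28, with death scored 0, by a within-pair rank test such as the Wilcoxon signed-rank test on twin differences. Clinical data collection already lists the mode of respiratory support over the first 28 days. This assumes that the mode is recorded day by day.
2. **Extubation and weaning to room air:** replace plain Kaplan–Meier with cumulative incidence, taking death as a competing event. The planned plots already need the event times.
3. **Raw durations, antibiotic days, hospital stay and expenses:** report descriptively by arm, beside the number of deaths, without a significance claim. Label any survivors-only summary as such.

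Days alive and out of hospital to the 40-week visit should not be adopted on the present data list. That measure needs every readmission, and Follow-up records only those for pneumonia.

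The cost is analysis wording, with no added infants or visits. The downside is that ventilator-free days mix death with duration, so deaths and ventilator days in survivors must both be shown beside the composite.
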